**Fig. 2 Fig2:**
[figure not shown]
Steps in obtaining lower lid margin sample. **a** Polyester tipped applicator swab to be swiped along the bilateral lower lid margin. **b** Snap the applicator into the sterile tube face down. **c** Cap the sample tube and stretch parafilm before storing

Study participants will collect their own rectal swabs. They will first collect the swab package with a cotton-tip swab and collection tube labeled “RECTAL,” as well as a biohazard bag to place the collection swab in, from the study coordinator. In a private location such as a restroom, the gloved participant will open the sterile flocked collection device and remove the swab from its wrapper without touching the cotton tip (Fig. 3a). Holding the swab between the thumb and forefinger for the best control, they can raise one foot onto the ledge of the toilet bowl and pull back the buttock with their left hand (Fig. 3b). They will then insert the cotton tip into the anus ½ to 1 inch deep (Fig. 3c) and rotate 360° twice (Fig. 3d) before gently removing. They will then place the soft tip into collection tube, snapping the neck of the swab, firmly closing the lid, and covering with parafilm (Fig. 2b, c). After placing the tube into an empty cell of the UNLINE 6 absorbent sheet they should dispose of the gloves and thoroughly wash their hands.

**Fig. 3 Fig3:**
[figure not shown]
Steps in obtaining rectal sample. **a** Gloved participant removes applicator while keeping the tip sterile. **b** Optimal positioning of applicator and body for sample collection. **c** Insertion of swab applicator ½ to 1 inch deep. **d** Rotate applicator 360° twice before removing

### Adverse events

All adverse events will be recorded and reported via the Adverse Event Reporting Form. Serious adverse event (SAE) collection begins after the patient has signed informed consent and has taken the first dose of the study medication. Study personnel must alert the medical monitor of any SAE within 24 h of investigator awareness of the event. Alerts issued via telephone are to be immediately followed with official notification on the Serious Adverse Event Reporting form. All serious or unexpected Adverse Events judged to be definitely, possibly, or probably related to study participation will be reported to the UCSF Committee on Human Research within 5 working days of their occurrence. Causality of the adverse event will be determined by the study investigators and the Data safety monitoring committee. Participants will be compensated if harmed.

### Data collection, management, and monitoring

Demographic data will be collected on enrolled study participants including ocular conditions, age, and gender. Collected sample material will be de-identified and analyzed in aggregate. Collected data will be recorded and managed electronically using REDCap electronic data capture tools hosted at the University of California, San Francisco. All devices used for electronic data collection will be password-protected, as will the mobile application itself. To assure data quality, we will follow NIH and UCSF guidance on data management. We aim to have internal validity checks, scripts for independently reproducible data processing workflow, and document datasets in codebooks. There will be range checks for all data points and data monitoring reports to flag outliers for possible data queries. Missing or incomplete data will be noted in the data collection tool and we will utilize what is possible for an intention-to-treat analysis. We will provide the sample size (*n*) for each data point for transparency in variation.

Study data will only be accessible by study team members and investigators during the duration of the trial to protect confidentiality. Upon completion of the trial, de-identified data will be available upon request.

### Study oversight

A Data and Safety Monitoring Committee (DMSC) created before the study begins will provide independent oversight of data quality and participant safety at annual committee meetings. The committee will review the number of patients and any significant adverse events. If necessary, the study analyst will provide unmasked treatment assignment to the committee. The DSMC will recommend modifications to the study protocol as necessary. Major protocol changes will be reported to the DSMC and Institutional Review Board (IRB) as required. Important protocol amendments will be communicated to all parties including the study team and trial participants via secure email.

### Statistical considerations

The primary analysis for AMR outcomes will be ANOVA to compare determinants of resistance to doxycycline across the three study arms. Power estimates for a difference in the overall microbiome composition between Arms A and B (L1-norm PERMANOVA) are more difficult, but it is worth noting that a similar design found significant differences in the gut microbiome after oral azithromycin [11]. Individual organisms will be compared between arms using a Benjamin-Hochberg False Discovery Rate of 5%, with results considered exploratory. Both overall composition and individual species will be compared using stool and lower lid specimens. In addition, comparison of the host immune response in the lower lid between arms will be exploratory, as we do not have previous estimates of the necessary standard deviation. Although, note, this study will allow an estimate of that standard deviation for future studies.

All primary analyses will be intention-to-treat. Patients that do not attend their scheduled follow-up visits will be contacted by the study coordinator the following day via phone and offered rescheduling. Repeated attempts will be made weekly for 4 weeks to contact patients lost to follow-up. Patients who discontinue one of the study treatments due to intolerability or side effects will be observed until the end of the study period if willing to return.

An interim analysis for efficacy is not planned for this trial given a small sample size.

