## Methods

### Study design

The Ocular Rosacea microBiome Study (ORBS) is a three-armed, parallel, randomized, masked, placebo-controlled clinical trial. Participants with a diagnosis of symptomatic ocular rosacea (*n* = 50) at the University of California, San Francisco in San Francisco, California, United States, will be prospectively enrolled and randomized to one of three arms in a 2:2:1 fashion. (1) Arm A, a SDD dose of doxycycline (40 mg) taken for 8 weeks; (2) Arm B, an antibiotic dose of doxycycline (200 mg) taken for 8 weeks; and (3) Arm C, a placebo pill taken for 8 weeks. The trial will begin enrollment in December 2022. This protocol adheres to the Standard Protocol Items: Recommendations for Interventional Trials (SPIRIT) guidelines (Supplementary Table S1) and is registered on clinicaltrials.org (NCT05296837) [9]. This study was reviewed and approved by the Institutional Review Board at the University of California, San Francisco (21–34725) and will be done in accordance with the Declaration of Helsinki.

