### Intervention and sample size

The study coordinator will offer a sealed container to each participant during their primary visit. Each day’s dose will be marked in individual AM/PM packets. The coordinator will instruct the patients to take both doses, AM and PM, daily for 8 weeks. Participants taking 40 mg doxycycline will be taking one 20 mg doxycycline pill twice a day. Participants taking 200 mg doxycycline will be taking 100 mg twice a day. Participants allocated to placebo will be taking a placebo pill twice daily. The initial dose will not be offered under clinical observation as the pills for each study arm will look different and can unmask the participant to the study team. Participants will bring medication to all follow-up visits, compliance will be monitored by pill count performed by the study monitor. Monitoring for systemic side effects will be done at study follow-up visits via a questionnaire. We will not take objective measurements of adherence such as blood levels due to inefficiency and cost in this modest sample cohort.

We estimate that twenty patients per arm will provide over 80% power to detect a twofold increase in tetracycline resistance genetic determinants between Arms A and B, assuming the standard deviation in read number found previously, allowing for 10% dropout, and correcting for baseline [10]. As a secondary analysis, we estimate that twenty patients in Arm A and ten in Arm C will provide over 80% power to detect a three-fold increase in tetracycline resistance genetic determinants.

We estimate that twenty patients per arm will provide over 80% power to detect a difference between Arms A and B in Shannon’s diversity effective number of 2 (from an effective number of 10. That is, 10 to 8 or 10 to 12 effective number), assuming 10% drop-out and a standard deviation in the effective number of 1.9, found in two previous studies [11, 12]. As a sensitivity analysis, we anticipate similar power using Simpson’s diversity (again, expressed as an effective number).

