### Outcomes assessment, schedule, and procedures

The primary outcome of interest is comparing the load, a quantitative measure, of AMR genetic determinants in lower lid and rectal swab samples between arms A (SDD dose) and arm B (placebo) when corrected for baseline. The secondary outcome of interest is microbiome diversity of the ocular surface and gut through Shannon’s Index and Simpson’s index. Other exploratory outcomes include comparative analysis of (1) host conjunctiva inflammasome expression; (2) Ocular Surface Disease Index (OSDI), with scores ranging from 0 to 100 with higher scores indicating greater symptom severity; and (3) TBUT scores with numbers representing how many seconds after a full blink a discontinuity in the tear film appears. A normal tear breakup time is greater than 10 s of tear stability between blinks. All outcomes will be compared between the three study arms, corrected for baseline. Using R statistics tool, we will use ANOVA and chi-squared to measure aggregate quantitative and distributive qualitative values respectively in each arm and compare at the 4-week, 8-week, and 4-month mark. Both primary and secondary outcome analysis will emphasize differences noted at 4 months between study arms when corrected for baseline.

Participants will be seen for four approximately 40-min visits over the course of the study: at baseline, 4 weeks, 8 weeks, and once 4 months after their last dose of study medication. The four-week visit will be 25–35 days after the initial visit, the 8-week visit 49–63 days after the initial visit, and four months 90–150 days after the initial visit. Participants will undergo ocular evaluation at every visit as well as have a lower lid margin swabs from each eye and a rectal swab collected at baseline, 8 weeks, and 3 to 6 months after the first dose of study medication. Table 1 summarizes the procedure schedule for each visit under SPIRIT guidelines [9].

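### The primary test (three-arm ANOVA), the contrast named as primary outcome and the contrast that was powered are three different things, and a significant F would not show whether SDD differs from placebo

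*Protocol article*

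**What the plan says.** Four places in the protocol article bear on the primary AMR comparison.

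- **Statistical considerations** fixes the test: "The primary analysis for AMR outcomes will be ANOVA to compare determinants of resistance to doxycycline across the three study arms".
- **Outcomes assessment, schedule, and procedures** fixes the primary outcome as a single comparison of AMR load "between arms A (SDD dose) and arm B (placebo) when corrected for baseline". It then says that all outcomes are compared across the three arms with baseline correction, by ANOVA for quantitative values.
- **Study design** defines the arms: "Arm B, an antibiotic dose of doxycycline (200 mg) taken for 8 weeks" and "Arm C, a placebo pill taken for 8 weeks". Arm A is 40 mg.
- **Intervention and sample size** makes the power claim: "twenty patients per arm will provide over 80% power to detect a twofold increase in tetracycline resistance genetic determinants between Arms A and B". It bases this on an SD taken from an earlier study, 10% dropout and baseline correction. Arm A v Arm C (20 v 10) is labelled secondary and powered for a threefold increase. Neither the SD nor alpha is given.

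The Introduction sets the question: whether the 40 mg dose really leaves the microbiome and resistance unaffected. It hypothesizes that both doses raise resistance expression over placebo.

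**The concern.** The F test asks whether any of three means differ. The outcome definition asks about one pair, and the power statement is about a pair too. The label conflict leaves it unclear whether these are the same pair: read by letter, the primary outcome is SDD v 200 mg; read by description, it is SDD v placebo.

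Two things are at stake. First, a significant primary result could arise with SDD identical to placebo, so it would not answer the question in the Introduction. The pairwise comparison used to interpret it could then be chosen after the data are seen. Second, the article states no power for the test it calls primary.

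**Working it through.** **Inputs from the article.** Allocation is 20/20/10 with 10% dropout, giving 18/18/9 evaluable. Effects are twofold (ln 2 = 0.693) for A v B and threefold (ln 3 = 1.099) for A v C. The Shannon statement uses a difference of 2 and SD 1.9.

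**Assumptions.** Two-sided alpha 0.05, log-normal load and equal variances. The SD is the residual SD on the natural-log scale after baseline correction, and it is varied because the article does not give it.

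**Step 1. Are the stated powers two-group calculations?** The Shannon statement is the one that can be reproduced. Noncentrality is 2 / (1.9 × √(1/18 + 1/18)) = 3.16. On 34 df this gives 86.6% power (88.5% by normal approximation), consistent with the stated over 80%.

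**Step 2. Largest SD compatible with the AMR claim.** The AMR figure cannot be reproduced without its SD. Solving the two-sample t-test (18 v 18) for exactly 80% power at ln 2 gives SD 0.721: 0.693 / (0.721 × √(2/18)) = 2.88. A normal approximation would give 0.742.

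**Step 3. Power of the F test.** Noncentrality is λ = Σ nᵢ(μᵢ − μ̄)² / σ², with μ̄ the weighted mean, on 2 and 42 df (critical value 3.22). With σ² = 0.721² = 0.520, (ln 2)² = 0.480 and (ln 3)² = 1.207:

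| True pattern | λ | F power |
|---|---|---|
| A–B twofold, placebo equal to A or B | 10.8 × 0.480 / 0.520 = 9.98 | 78.4% |
| A–B twofold, placebo midway (worst case) | 9 × 0.480 / 0.520 = 8.32 | 70.2% |
| A–B twofold, placebo a further twofold below A | 25.2 × 0.480 / 0.520 = 23.3 | 99.1% |
| A = B, both twofold over placebo | 7.2 × 0.480 / 0.520 = 6.65 | 59.8% |
| A = B, both threefold over placebo | 7.2 × 1.207 / 0.520 = 16.7 | 95.1% |
| A = placebo, B threefold higher | 10.8 × 1.207 / 0.520 = 25.1 | 99.4% |

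The multipliers are Σ nᵢ(cᵢ − c̄)² for the pattern of means. For example, 27 v 18 patients gives 27 × 18 / 45 = 10.8, and 36 v 9 gives 36 × 9 / 45 = 7.2.

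**Step 4. Sensitivity to the SD (A–B twofold).**

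| ln-SD | A v B t-test | F, placebo = A or B | F, placebo midway |
|---|---|---|---|
| 0.5 | 98.1% | 98.2% | 95.8% |
| 0.6 | 92.0% | 91.7% | 85.8% |
| 0.7 | 82.3% | 80.9% | 73.0% |
| 0.721 | 80.0% | 78.4% | 70.2% |

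**Step 5. SDD v placebo as a pairwise t-test (18 v 9).** At SD 0.721, power is 61.9% for twofold and 94.8% for threefold. At SD 0.6, power for twofold is 77.6%.

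**The case against.** A fair defence has four parts.

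- **Power.** A reader might infer that the ANOVA fails to reach 80%. The article does not support that. Its SD is missing, and 0.721 is the boundary case, whereas the claim is for more than 80%. By SD 0.6 the F test exceeds 80% even with placebo midway, and at 0.721 it reaches 99% if placebo lies well below A. The 60% figure uses a twofold effect over placebo, which the article does not power; at its own threefold effect the figure is 95%. This objection stands.
- **Baseline.** A reader might infer that the ANOVA ignores baseline. It does not: the outcomes section applies baseline correction to the three-arm comparisons immediately before naming ANOVA. The form of correction may be left to the SAP. For the same reason, no gain from ANCOVA should be claimed, since the stated power already includes the correction.
- **Scale.** A reader might infer that skewed counts will be analyzed untransformed and that power is lost. The article does not say so.
- **SDD v placebo is in the plan.** It is powered as a secondary comparison, and the outcomes section may intend it as primary. This is true, but it sharpens the inconsistency: if it is primary, the stated primary test does not isolate it and its power appears only under a secondary label.

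What remains is not detail deferred to an SAP. The article itself names a test, a contrast and a power, and they disagree.

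**Conclusion.** The point holds as an inconsistency with consequences for interpretation. The omnibus F is neither the contrast defined as primary outcome nor the one that was powered, and the arm label leaves that contrast ambiguous. If SDD equals placebo and 200 mg is threefold higher, the F test is significant 99.4% of the time at ln-SD 0.721, so a positive primary result need say nothing about SDD.

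On power, the supported conclusion is only that the stated figure does not transfer. For a twofold A–B difference, F power could be as low as about 70% if pairwise power is just at 80%, and is comfortably above 80% if the SD is smaller or placebo lies well below A. These figures rest on the assumed alpha, log-normal load, equal variances and 18/18/9 evaluable.

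**What to change.** 1. Reconcile the Arm B label in the outcomes section with the study design.
2. Replace the omnibus ANOVA as primary with one pre-named pairwise contrast from the baseline-corrected three-arm model, reported as a fold ratio with 95% CI. SDD v placebo matches the question in the Introduction.
3. Keep the three-arm F test as supportive.
4. Restate power for the chosen contrast, giving its SD, scale and alpha.

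No new data are needed, but this is more than a wording change. Making SDD v placebo primary promotes a comparison that the article calls secondary and powers only for a threefold increase. For a twofold increase its power is about 62% at ln-SD 0.721 and 78% at 0.6. If the sponsor instead keeps A v B as primary, the stated power applies to it, but the primary result will compare two doses and will not show whether SDD differs from placebo. The article should then say so.

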## Discussion

In most clinical scenarios, long-term antibiotic dosing is not recommended due to the risk of antimicrobial resistance selection [13–17]. For pediatric patients with recurrent urinary tract infections (UTIs), long-term antibiotic prophylaxis increases the risk of UTIs with antibiotic-resistant strains without significantly reducing renal scarring [18]. Long-term, low-dose macrolide treatment for pediatric patients with chronic airway diseases such as severe asthma and cystic fibrosis (CF) may have clinically beneficial outcomes, but at the cost of widespread macrolide resistance [19]. With adults, 90% of *E. coli* urinary isolates were reported resistant to trimethoprim- sulfamethoxazole within 1 month of prophylactic use and azithromycin resistance appears to be significant when used continuously to prevent acute exacerbations of chronic obstructive pulmonary disease [15, 20]. Curiously, long-term low dosing of doxycycline for ocular rosacea appears to be the universally accepted practice as this strategy is believed to bypass antimicrobial resistance, but investigation into conformation of this fact with more sophisticated genomic tools is lacking [2–4].

We note that antibiotic susceptibility determined by culture-based techniques may not fully represent the resistance profile [21]. Growing phenotypically resistant cultures in petri dishes only reveals the bacterial profile grown in culture, not the complete colonization and/ or infection of a patients’ sampled system [22]. A study using advanced genomic sequencing methods found that the presence of antibiotic multidrug resistance within the CF airway microbiome was associated with decreased microbial diversity as measured by Simpson’s index [21]. Even in cohorts of healthy patients, virome sequencing showed an expansion of antibiotic-specific resistance genes in the gut microbiome persisting three months after a 1-week course of antibiotics [23, 24]. Investigation using advanced genomic sequencing to confirm whether or not expression of AMR variants are altered in other microbiota, namely the ocular surface and the gut, has the potential to alter ocular rosacea treatment recommendations.

These results will enhance our understanding of the overall systemic impact of long-term systemic sub-microbial antibiotic dosing for the treatment of chronic recurrent ocular inflammatory diseases.

## Trial status

This study was registered on ClinicalTrials.gov on March 25, 2022 (NCT05296837). The current protocol is version 3 on April 27, 2022. There is no associated registered data set. Recruitment is estimated to begin in December 2022. The trial is estimated to be completed by December 30, 2023, and the study completed by June 31, 2024.

## Data Availability

Trial results will be presented at local, national, and international meetings and submitted to peer-reviewed journals for publication. Project involvement will determine authorship, no professional writers are anticipated to be hired. De-identified trial data will be made publicly available after publication of primary outcomes.

## Abbreviations

AE: Adverse Event
AMR: Antimicrobial Resistance
CF: Cystic Fibrosis
DSMC: Data Safety and Monitoring Committee
IOP: Intraocular Pressure
OSDI: Ocular Surface Disease Index
RNA-seq: RNA Deep Sequencing
SAE: Serious Adverse Event
SDD: Sub-microbial Dose Doxycycline
TBUT: Tear Breakup Time
UCSF: University of California, San Francisco
UTI: Urinary Tract Infection
